**Fig. 2 Fig2:**
[figure not shown]
Overview of the study design with the three laboratory assessments (t0, t1, t2), the 6-week waitlist-control and Reality DTx^®^ intervention periods, the counterbalancing of AR glasses over participants, and the weekly telephone calls to personalise participants’ gait-and-balance exergaming schedule

In between gait-laboratory visits 1 and 2 (i.e. t0 and t1, delineating the 6-week waitlist-control period), participants will not receive any instructions or training regarding Reality DTx^®^ and will carry out their activities and care as usual. The Reality DTx^®^ AR therapeutic exergaming intervention is intended as an intervention additional to usual care. Therefore, there will be no restrictions to care as usual during the 6-week intervention period, except for changing the dosage of medication (see exclusion criteria). Usual care and potential changes therein will be reported over the 6-week waitlist-control period as well as over the 6-week Reality DTx^®^ intervention period. In between laboratory visits 2 and 3 (i.e. t1 and t2, delineating the 6-week Reality DTx^®^ intervention period), participants will independently use Reality DTx^®^, remotely monitored and prescribed personalised AR gait-and-balance therapeutic exergaming in their home environment.

#### Laboratory assessments (t0, t1, t2)

Table 1 provides an overview of the data collected during the baseline (t0), pre-intervention (t1), and post-intervention (t2) laboratory assessments, which include demographic data, questionnaire data, and standard clinical gait-and-balance test data. Participants will also undergo a gait assessment on the Interactive Walkway (IWW), a validated instrumented 10-m walkway for markerless full-body 3D motion registration [31–35] to assess gait parameters during a standard 10-m walk test (e.g. walking speed, step length, cadence) and to perform a targeted walking-related fall-risk assessment, focusing on walking-adaptability tasks using projections on the walkway to elicit step or gait adjustments for precision stepping, sudden turning, sudden obstacle avoidance, and narrow-beam walking [32, 34, 35]. The order of the gait-and-balance tests (i.e. TUG, FTSTS, Mini-BESTest, and IWW) will be counterbalanced over participants but remains fixed per participant over t0, t1, and t2 laboratory visits.

During baseline (t0) and pre-intervention (t1) assessments, participants will get the opportunity to practice and familiarise themselves with the Reality DTx^®^ gait-and-balance exergames. After the post-intervention assessment (t2), participants will be asked to participate in a semi-structured scripted on-site or telephone interview (as detailed in Additional file 5) to evaluate Reality DTx^®^ therapy including various feasibility aspects regarding usability, safety, perceived efficacy, performance, context-specific factors of the training, FITT principles, the commercial potential, and to gather feedback for improvements. The interview is partly based on the theoretical framework of acceptability [36, 37]. The interview data is supplemented with existing scales for user experience [38], intrinsic motivation [39], and acceptability [40]. After this final evaluation interview, participants will receive an individual report about their performance during the Reality DTx^®^ exergaming intervention and their gait-and-balance test scores over t0, t1, and t2.

Participants are invited to participate in an optional fourth lab visit, somewhere during the intervention period, for a stand-alone experiment on the gait-modifying effects of AR cues and to assess concurrent validity and test–retest reliability of the clinical outcome measures of gait and balance derived from the AR glasses. This optional laboratory visit is beyond the scope of the feasibility study and will therefore not be addressed further in this protocol.

#### Home visit

A researcher will visit participants’ homes to set up the AR glasses (either HoloLens 2 or Magic Leap 2) and define a safe space for home-based gait-and-balance exergaming. Both AR glasses are non-occluding (see-through lenses) and use a form of simultaneous localisation and mapping (SLAM) to anchor holographic content in the real world, which allows users to control the Reality DTx^®^ software using hand tracking (e.g. pressing a holographic button) and voice commands. The AR glasses differ in weight (HoloLens 2 is untethered and weighs 566 grammes which is heavier than the Magic Leap 2 which is a tethered device (260 grammes, at the expense of a cable connecting the glasses to a waist-worn computer and battery pack)), AR field of view (double for Magic Leap), hand-tracking quality (better for HoloLens than for Magic Leap, which comes with a hand-held controller; in the proposed study, participants will be encouraged to use their hands to control Reality DTx^®^ instead of the controller), battery life (HoloLens 2–3 h, Magic Leap 3.5 h), and corrective eyewear (HoloLens can be worn over individual’s prescription glasses, for Magic Leap prescription lenses can be ordered and inserted).

During this home visit, participants will receive printed and oral instructions on how to (safely) use the AR glasses and will then do a second supervised Reality DTx^®^ gait-and-balance exergaming session with the researcher. Participants receive a diary to rate their experience after every exergaming session on a 5-point Likert scale. They will also be asked to administer the exercise day and how many times they played each therapeutic exergame. Potential falls [41] and technical issues are also noted. Participants may write down any points they want to discuss during the weekly telephone call (see Additional file 2 for details on the diary).

#### Remote monitoring of gait-and-balance exergaming adherence and performance and telephone calls to personalise the remote prescription of exergaming schedules

The Reality DTx^®^ web portal is designed by Strolll as an online e-portal for healthcare professionals to prescribe, monitor, and adjust the Reality DTx^®^ gait-and-balance exergaming intervention and to remotely track the participant’s progress (Fig. 3). In the proposed study, the web portal will be used to remotely prescribe personalised exergaming schedules on a weekly basis (Fig. 3A) and to monitor the participant’s adherence and performance remotely (Fig. 3B, C). The initial training schedule (frequency, difficulty, type, and duration) is created by the researchers based on the supervised Reality DTx^®^ familiarisation and practice sessions during the laboratory visits (t0, t1) and home visit. The training schedule will be adjusted by the researcher every week through the Reality DTx^®^ web portal. Adjustments are made in close collaboration with the participants based on their subjective experiences evaluated during the weekly semi-structured telephone call (see Additional file 3) and based on the (objective) adherence (performed gait-and-balance exergames as a percentage of the prescribed gait-and-balance exergames) and performance (the score per game) scores available in the Reality DTx^®^ web portal. The weekly telephone calls will also be used to ask if participants experienced any technical issues (usability flags) or adverse events (safety flags).

**Fig. 3 Fig3:**
[figure not shown]
Snapshots of the web portal to remotely prescribe (**A**) and monitor (**B **and **C**) gait-and-balance exergames. Please see Table 2 for a description of all adjustable Reality DTx^®^ gait-and-balance exergaming elements per game

### Participants and recruitment

We aim to recruit 24 participants with PD. Recruitment started in December 2022. According to planning, the final post-intervention assessment (t2) will be in July 2023. Participants will be recruited using various channels: through regular clinical care (i.e. via neurologists and physiotherapists in our network) and via presentations at various Parkinson community groups hosted by the Dutch Parkinson Association and through the website of the Dutch Parkinson Association. People who are interested in participating will receive detailed written information about the study before consenting to participate in this study. The information letter was drafted in consultation with patient representatives of the Dutch Parkinson Association and approved by the medical ethical committee. At least 1 week after receiving the information letter, potential participants will be contacted through telephone calls by the researchers to check whether they understood the information letter and to answer any questions. After affirming that a potential participant is willing to participate, the following eligibility criteria will be checked.

#### Inclusion criteria

To be eligible to participate in this study, participants must meet the following criteria: 18 years or older, have command of the Dutch language, diagnosed with PD according to the UK PD Brain Bank criteria (stages 2–4 on the Hoehn and Yahr scale), and experience bothersome gait and/or balance impairments based on self-report (i.e. negatively affecting their ability to perform their usual daily activities).

#### Exclusion criteria

Potential participants will be excluded from participation in this study when meeting any of the following criteria: inability to comply with the protocol, i.e. additional neurological diseases and/or orthopaedic problems seriously interfering with gait-and-balance function, insufficient physical capacity or cognitive/communicative inability to understand instructions and participate in the tests (as observed by the researchers), visual or hearing impairments (after corrective aids), severe visual hallucinations or illusions, inability to walk independently for 30 min, and no stable dosages of dopaminergic medication.

After passing the telephonic eligibility screening, participants will be invited to the gait laboratory where they will sign for written informed consent (see Additional file 1) before the start of the baseline assessment. They will be informed explicitly about the possibility to be excluded from the study after baseline based on an objective assessment of the eligibility criteria and/or serious safety concerns. To this end, participants’ demographics will be documented to characterise the study population in terms of age, gender, disease duration, current medication use (type, dose, and frequency), and scores on Movement Disorders Society Unified Parkinson Disease Rating Scale (MDS-UPDRS), Montreal Cognitive Assessment (MoCA) and falls history. Safety and eligibility concerns will be based on performed motor/cognitive/falls-risk assessments as well as a supervised Reality DTx^®^ gait-and-balance exergaming session during t0. The entire baseline assessment session will be recorded on video to discuss participants’ safety and eligibility concerns among the researchers, who will then jointly decide on exclusion or not. Reasons for potential exclusion will be documented as part of the feasibility evaluation.

### Randomisation, blinding, and treatment allocation

In this waitlist-controlled clinical feasibility study, all participants will receive Reality DTx^®^, a home-based remotely monitored and prescribed personalised AR gait-and-balance therapeutic exergaming intervention. The intervention will be delivered through two different types of AR glasses (i.e. HoloLens 2 or Magic Leap 2), which will be distributed over participants using block randomisation in blocks of four and at the end of recruitment in blocks of two to increase the likelihood for equal groups given the potential exclusion of participants after the baseline assessment and potential unforeseen recruitment issues (executed by LH and EH). Hence, half of the participants will receive the Reality DTx^®^ intervention on HoloLens 2 and the other half on Magic Leap 2. The participants and researchers will not be blinded for the allocated AR glasses.

### Sample size

For the proposed study, in which Reality DTx^®^ therapeutic gait-and-balance exergaming will for the first time be used independently at home, we will include a convenience sample of 24 participants to evaluate its initial feasibility (safety, adherence, and user experience) and potential efficacy for improving gait and balance. This sample size fits this type of study and is logistically feasible given the associated number of laboratory visits (72), weekly telephone calls (120), and home visits (24) vis-à-vis the availability of the gait laboratory and personnel, project duration, and funding. In addition, a sample of 24 participants is sufficient to evaluate the potential efficacy of this exergaming intervention. That is, with 95% power, a one-tailed alpha error of 5% and an expected minimum improvement of 1.63 s on the Timed Up-and-Go test (i.e. smallest detectable difference [42], a sample size of 18 is required to detect an effect with an effect size of 0.815 (Cohen’s *d* statistic; SD over repeated measurements 2.0 s [43]). This a priori required sample size calculation for differences between two dependent means was calculated with G*Power 3.1.9.7.

### Outcomes

#### Primary study parameter

The primary study parameters to evaluate the home-based AR gait-and-balance exergaming intervention are feasibility and potential efficacy:

Feasibility is expressed in:Safety, i.e. the number of (serious) adverse events categorised as falls, near falls, dizziness, eyestrain, headache, or other [29, 30] associated with the exergaming intervention, as administered during weekly semi-structured telephone calls and the Reality DTx^®^ evaluation interview. A fall is defined as a slip or trip in which one loses balance and lands on the floor, ground, or lower level [41]. A near fall is defined as a slip, trip, or loss of balance that would result in a fall if adequate recovery mechanisms were not activated [41].Adherence, i.e. compliance to the prescribed personalised exergaming intervention as measured in frequency (ratio of performed to prescribed number of exergaming sessions), time (i.e. duration, the ratio of performed to prescribed exergaming minutes per session), and repetitions (number of performed in-game functional motor tasks like number of squats, metres walked, number of functional reaches, …) as recorded in the web portal on a weekly basis throughout the 6-week Reality DTx^®^ intervention period, as well as the number of dropout participants, including reason(s) for withdrawal if specified,User experience, i.e. (1) usability based on the Dutch 26-item User-Experience Questionnaire [38] administered at t2, (2) the number and nature of the reported technological issues (e.g. AR glasses, software, Wi-Fi) during the 6-week intervention period, (3) acceptability based on a previously used intervention evaluation Likert-scale questionnaire [40] (as specified in Additional file 4) at t2, and (4) a semi-structured evaluation interview (as described previously and specified in Additional file 5) at t2 [36, 37].

Potential efficacy of the Reality DTx^®^ intervention will be explored using gait-and-balance outcome measures from the following standard clinical and IWW gait-and-balance tests, all assessed at all three timepoints (t0, t1, and t2, see Table 1):Balance: Mini Balance Evaluation Systems Test [44],Functional mobility: Timed Up-and-Go test (s) [45],Gait mobility: Lindop Parkinson’s Physiotherapy Assessment Scale [46],Walking adaptability: Targeted walking-related fall-risk assessment based on outcome measures of walking adaptability as determined with the IWW (obstacle avoidance margins and success rates and stepping accuracy and walking speed during goal-directed stepping) [31–35].

#### Secondary study parameters

Secondary study parameters include additional gait-and-balance outcome measures and patient-reported outcome or experience measures (PROMs/PREMs) to further evaluate the feasibility and potential efficacy, assessed online or in the laboratory at three time points (t0, t1, and t2, see Table 1):Lower limb strength: Five Times Sit to Stand Test [47],Motor disease severity: Scores of Movement Disorders Society Unified Parkinson Disease Rating Scale (MDS-UPDRS) [48],Presence of freezing of gait: New Freezing of Gait Questionnaire [49],Balance confidence: Activities-Specific Balance Confidence Scale [50],Fear of falling: Falls Efficacy Scale International [51],Physical activity: Physical Activity Scale for the Elderly [52],Quality of life: Parkinson’s Disease Questionnaire [53],

assessed online after the 6-week Reality DTx^®^ intervention period:Intrinsic motivation: Intrinsic Motivation Inventory [39, 54].

### Discontinuation or modification of allocated intervention

Participants can leave the study at any time for any reason if they wish to do so without any consequences. The investigator can decide to withdraw a participant from the study for urgent medical reasons or when medication dosage is changed during the study. Participants who drop out or who withdraw before commencing the intervention (that is, before the home visit) will be replaced by a newly recruited participant. Reasons for dropout or withdrawal will be collected. In case of unforeseen circumstances such as illness, technical issues or holidays that interrupt the planned training period, and if the participant is physically able and willing to resume the training once the unforeseen circumstance has been resolved, the training period will be extended to compensate for the missed days.

### Premature termination of the study

The study will be terminated prematurely if serious adverse events (SAE, like injurious falls) related to the Reality DTx^®^ intervention are reported for more than two participants. Liability insurance is in place in accordance with the legal requirements in The Netherlands, specifically Article 7 of the Medical Research Involving Human Subjects Act (in Dutch: Wet Medisch-wetenschappelijk Onderzoek met Mensen, WMO). This insurance provides cover for damage to research participants through injury or death caused by the study. The insurance applies to the damage that becomes apparent during the study or within 4 years after the end of the study.

### Statistical analysis

Data analysis will be performed in JASP [55]. Missing data will be excluded analysis-by-analysis. The Reality DTx^®^ semi-structured evaluation interview will be analysed qualitatively.

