#### Feasibility of Reality DTx^®^

Study parameters to evaluate clinical feasibility (safety, adherence, user experience) of the Reality DTx^®^ intervention will be compared between the two groups (HoloLens 2, Magic Leap 2) using independent-sample *t*-tests. The Shapiro–Wilk test will be used to check for normality. If the data is not normally distributed, the Mann–Whitney *U*-test will be used. Weekly scores of feasibility parameters (e.g. adherence scores over the intervention period) will undergo 2 (between-subjects factor Group: HoloLens 2 vs Magic Leap 2) × 6 (within-subjects factor Weeks: week 1 to 6) mixed ANOVA.

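### Complete-case mixed ANOVAs leave out participants who stop after the home visit, which may inflate the adherence ratio and, if loss relates to outcome, bias the efficacy estimate

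*Protocol article*

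**What the plan says.** The missing-data rule is one sentence under Statistical analysis: "Missing data will be excluded analysis-by-analysis". The methods it governs follow in the next two subsections. Weekly feasibility scores, with adherence as the example, go into an ANOVA of Group by "within-subjects factor Weeks: week 1 to 6) mixed ANOVA". Efficacy outcomes go into a mixed ANOVA of Group by Time, with Time at t0, t1 and t2.

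Under Primary study parameter, adherence includes "frequency (ratio of performed to prescribed number of exergaming sessions"), a similar ratio for minutes, and a count of repetitions, all recorded weekly in the web portal. The same item also lists how many people drop out and why.

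Under Discontinuation or modification of allocated intervention, someone lost before the home visit "will be replaced by a newly recruited participant"; nothing similar is stated for later losses. The section adds: "Reasons for dropout or withdrawal will be collected". The investigator may also withdraw a participant for urgent medical reasons "or when medication dosage is changed during the study". The section gives no criterion for using that option and does not mention a t2 visit for people who are withdrawn.

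**The concern.** A classical repeated-measures ANOVA cannot use a participant with an empty cell. Under the stated rule, a person who leaves in week 3 is absent from the whole 2 × 6 adherence analysis, including the two weeks that were recorded. A person without t2 is absent from the whole 2 × 3 efficacy analysis, including t0 and t1.

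For adherence, permanent stopping is the extreme of the thing being measured, so leaving stoppers out tends to flatter the ratio. For efficacy, the analysed set is people who stayed, and staying may be related to how they were doing.

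Adherence and potential efficacy are both primary parameters. Under Future steps after this feasibility trial, the results are meant to guide the sample size and outcome choice of later randomised trials, so any optimism would carry over into them.

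**Working it through.** **1. The plan's own figure.** Sample size section: improvement 1.63 s on the Timed Up-and-Go (TUG), SD 2.0 s, one-tailed alpha 5%, power 95%. d = 1.63/2.0 = 0.815. Exact paired t-test power (noncentral t, df = n − 1, noncentrality d·√n) first reaches 95% at n = 18 (power 0.953), as stated. Power is 0.987 with 24 analysed and 0.969 with 20. On the plan's own assumptions a few losses do not threaten power, so the question is bias.

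**2. Adherence.** Inputs: N = 24 and six weeks (protocol). Assumptions: adherence A = 0.80 in every week trained, k people stop for good after week w, weekly ratios are averaged, and later weeks count as zero.

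- Completers: A = 80%.
- All starters: [(24 − k)·A + k·A·w/6]/24.
- k = 3, w = 2: (21 × 0.80 + 3 × 0.80 × 2/6)/24 = (16.8 + 0.8)/24 = 73.3%.
- k = 4, w = 2: (20 × 0.80 + 4 × 0.80 × 2/6)/24 = (16.0 + 1.07)/24 = 71.1%.

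The overstatement is A·(k/24)·(1 − w/6). Over a wider range, still with A = 0.80:

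| Stoppers | Stop after week 3 | Stop after week 1 |
|---|---|---|
| 2 | 3 points | 6 points |
| 4 | 7 points | 11 points |
| 6 | 10 points | 17 points |

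The 80% does not depend on listwise deletion alone. The feasibility section also compares the two glasses groups by t-test or Mann–Whitney test. If stoppers enter that test with a ratio over the weeks they trained, they contribute 80% and the group figure still reads 80%.

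**3. Efficacy.** Simulation of 24 paired changes, mean 0, SD 2.0 s (used as the SD of the change, as the plan's calculation does), positive meaning improvement. k participants are removed according to a latent score with correlation ρ to their change, and the rest are tested by a one-sided paired t-test at 5%, a simplified stand-in for the planned ANOVA.

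| Lost | ρ = 0 | ρ = 0.3 to 0.5 | The k worst lost |
|---|---|---|---|
| 2 | bias 0, error 0.05 | +0.10 to +0.16 s, error 0.08 to 0.11 | +0.32 s |
| 4 | bias 0, error 0.05 | +0.17 to +0.29 s, error 0.11 to 0.17 | +0.58 s |
| 6 | bias 0, error 0.05 | +0.25 to +0.41 s, error 0.13 to 0.23 | +0.82 s |

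The last column is an upper bound.

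**4. Direction under medication change.** Suppose 4 of 24 worsen by 2 s, have their dosage changed, and the other 20 average 0. Withdrawing the four gives a mean of 0. Keeping them gives:

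- no gain from the change: 4 × (−2)/24 = −0.33 s, so withdrawal raises the estimate;
- a gain of 2 s: 4 × 0/24 = 0, so withdrawal makes no difference;
- a gain of 3 s: 4 × 1/24 = +0.17 s, so withdrawal lowers the estimate.

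**The case against.** A reader might infer that the plan removes dropouts from the adherence outcome and biases both adherence and efficacy upward. The protocol does not support that, for these reasons.

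- Dropout numbers and reasons are part of the adherence outcome, so a favourable ratio would stand beside them. This stands, although the count does not correct the ratio.
- Someone still enrolled with a prescription who does nothing already scores zero, and interrupted training is extended when the person can resume. This stands. The problem is confined to permanent leaving, where the text does not say how the remaining weeks count. Because schedules are set week by week, a person who has left may have no prescription, and scoring those weeks zero is one defensible definition among others.
- The t0 and t1 data of people lost at t2 are not discarded everywhere. The post hoc t0–t1 comparison is a separate analysis and keeps those pairs. This stands; the loss is from the 2 × 3 ANOVA.
- A dosage change is not the same as worsening, and withdrawal is optional. Stable dosing is an eligibility condition, and usual care is otherwise unrestricted, "except for changing the dosage of medication (see exclusion criteria"). With no concurrent untreated group, a dosage change that improves t2 would be counted as an intervention effect if the person were kept. This stands, and it is why no direction can be claimed for efficacy.
- A linear mixed model assumes data missing at random and does not cure loss driven by an unseen t2 result. This also stands. The model still uses visits that the ANOVA discards, and seeking t2 data addresses part of the rest.
- The protocol sets no adherence threshold that 73% rather than 80% would cross. True, but the figures are meant to inform later trials.

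**Conclusion.** The point holds as a risk of bias. The stated rule combined with the two mixed ANOVAs leaves out anyone who stops after the home visit and lacks later weeks or t2.

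If weeks after stopping are treated as missing, the performed-to-prescribed ratio is too high as a description of everyone who started: 80% against 73% or 71% for 3 or 4 stoppers after week 2, and 3 to 17 points for 2 to 6 stoppers after week 3 or week 1. These figures rest on an assumed 80% while training and on assumed dropout numbers.

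For efficacy, bias is zero if loss is unrelated to outcome, about +0.1 to +0.4 s on TUG if 2 to 6 losses are moderately related to worsening, and possibly downward if a dosage change would have improved t2. The stronger reading, that efficacy is biased upward, is not established.

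**What to change.** 1. **Adherence.** Report it for everyone who had the home visit, with weeks after permanent stopping counted as zero performed, beside the ratio while in training. Averaging weekly ratios avoids the need for a prescription after leaving.
2. **Efficacy model.** Replace the complete-case mixed ANOVA by a linear mixed model with Time, Group and Time × Group, using all available t0, t1 and t2 data. State that it assumes missing at random.
3. **Follow-up.** Invite people who stop training to the t2 visit where they agree. The 72 laboratory visits under Sample size are 24 × 3, so t2 for all 24 is already budgeted.
4. **Medication changes.** Show efficacy with and without any participants whose medication changed and who have t2 data. Which set is the main one is for the study team to decide and state, and whether a dosage change should lead to withdrawal is not judged here.

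Cost: a somewhat lower adherence figure and slightly more analysis work. Portal data up to stopping are recorded, and changes in usual care are already to be reported (Procedure).
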